\* **Pilot of Game Changers for CC prevention (GC-CCP):** With an R21, we did formative research to adapt the GC model for CC. Focus groups with women who had and had not screened for CC revealed that like the HIV context, stigma, knowledge, and disclosure were key factors for engagement in advocacy, and thus retained in the intervention model. Internalized stigma did not appear to be an impediment to CC screening per se, but rather stigma and fear acted more as barriers to CC screening disclosure (especially if screened positive), and procedures related to VIA and treatment (e.g., misconceptions that such procedures would harm the vagina and make a woman sterile). A 7-session version of GC-CCP was developed and tested in an RCT with 40 screened women (20 intervention, 20 control) as index participants, from whom 103 alters (58 intervention, 45 control) who had never screened for CC were recruited; all participants were followed for 6 months (with 96% retention). The intervention was feasible and acceptable: peer facilitators were trained to implement the sessions, and 19/20 intervention index participants attended every session.

**Intervention effects on CC screening, CC prevention advocacy, and related outcomes.** In multivariate models controlling for baseline measures of the dependent variable and sociodemographics, alters in the intervention group were much more likely to have been screened for CC at month 6 [64% vs. 16%; adj. OR (95% CI) = 12.13 (4.07, 36.16)], and a higher percentage of alters named in the network assessments of the index survey (360 alters across all index participants; none of whom were perceived to have ever been screened at baseline) were perceived by the index to have been screened at month 6 [57% vs. 14%; adj. beta (SE) = 0.40 (.07);  $p<.001$ ], compared to those in the control. Index participants who perceived an enrolled alter to have screened for CC at month 6, were correct 88% of time. Alters in the intervention arm also reported greater engagement in CC prevention advocacy, CC knowledge, and CC risk management, compared to control alters (all  $p$  values < .001). Intervention index participants reported greater CC prevention advocacy at month 6, as well as greater sharing of CC screening experience, CC knowledge, CC prevention advocacy self-efficacy, and CC risk management (most  $p$  values < .001), compared to index participants in the control group.

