formative research and pilot of GC-CCP. In the proposed study, we continue at the phase of **Preparation**: In Year 1, we will identify modifiable clinic and provider level barriers to easy access to CC screening at 4 study clinics [2 public, 2 private-not-for-profit (PNFP), one each in an urban and rural location]. To prepare the clinics for implementation, we will conduct feasible remediation of barriers and enhance usual care via provider training on the importance of recommending CC screening to clients. **Implementation**: At each clinic, 40 women screened for CC will be enrolled in the RCT as index participants (n=160 index) and randomized to the intervention (in two groups of 10) or wait-list control. Each index will recruit up to three (1st degree) alters (n~440 alters) at baseline who have not screened for CC; these index and alter participants will be followed up at months 6 and 12. At month 6, these alters will each recruit up to two (2nd degree) alters (n~800 alters) for a single phone interview. **Sustainment**: After the enrolled index participants receive the intervention, each clinic will continue to implement GC-CCP with clients not enrolled in the trial on a quarterly basis for an additional 2.5 years, with training and supervision tasks transferred to clinic staff. Using the RE-AIM framework, we will evaluate engagement in GC-CCP and CC advocacy (reach), alter CC screening (effectiveness), adoption into clinic operations, implementation outcomes (acceptability, feasibility, fidelity) and maintenance.

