## Statistical Analysis

**Power:** Assuming 220 1st degree alters per arm enroll, 10% attrition (month 6 retention in pilot was 96%; we have retained 90-94% over 12 months in past studies in Uganda), ICC=.01-.05 range to control for clustering within the alters of each index participant, and a 15% CC screening rate in control alters (based on pilot data): the effective sample size will be 200 (ICC=.05) or 216 (ICC=.01) per arm. If ICC=.01, we will be able to detect a small effect size (11 percentage point difference) in alter CC screening at month 12 (80% power; alpha = .05). If ICC=.05, the detectable effect size is 12 percentage point difference (or odds ratio of 2.0).

**Aim 1:** *Assess effects of GC-CCP on alter CC screening.* We will use an intent-to-treat approach. In addition to comparing the arms at baseline and months 6 and 12, we will apply logistic generalized mixed models to our repeated-measures data to examine intervention effects, using a time by arm interaction to assess differences between the arms over time. We will account for correlation among participants in the same intervention group, and among alters referred by the same index, by adjusting standard errors for statistical inference tests with a sandwich estimator. We will use imputation for item nonresponse and attrition weights to account for non-random dropouts using logistic regression. We will control for and examine interaction effects with index (e.g., age), alter (e.g., knowledge of index's CC screening), and intervention (sessions completed) variables.

**Aim 2:** The analysis for this aim is described in the Preparation and Sustainment phases.

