## **F. DATA SAFETY AND MONITORING PLAN**

### **I. Description of Study and Study Data**

This study is a partnership among RAND Corporation ([name] and [name], MPIs), Makerere School of Public Health ([name], MPI), African Palliative Care Association, Rays of Hope Hospice Jinja, and Indiana University at Bloomington. We will conduct a hybrid implementation-effectiveness randomized controlled trial (RCT) of *Game Changers for Cervical Cancer Prevention (GC-CCP)*, a 7-session peer-led group intervention that aims to empower and mobilize women who have screened for cervical cancer (CC) to be agents for CC screening and prevention in their social networks. For the RCT, we will recruit 160 screened women (index participants) across 4 clinics, randomizing 80 to the intervention and 80 to the usual care control condition. Each index participant will be asked to recruit up to 3 social network members (1st degree alters) who have never screened for CC to complete assessments (~440 total based on average of 2.75 alters recruited per index participant, 220/arm) over 12 months, to test intervention effects on alter uptake of CC screening. All participants will complete surveys at baseline, and 6- and 12-months post-baseline. At the

month 6 follow-up, first degree alters will be asked to recruit up to 2 of their social network members (2nd degree alters; ~ 800 total). Surveys of index and alter participants will include questions about CC screening, CC knowledge, CC stigma, and engagement in CC prevention advocacy. Data on alter CC screening and treatment will be extracted from medical records. All data will be collected and stored at the participating clinic sites initially, and then transferred to Makerere University School of Public Health; de-identified data will be transferred to RAND for data management and analysis.

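### The month-12 power statement borrows a month-6 pilot control rate and leaves out its own 10% attrition, so 11 points at ICC .01 has about 77% power, not 80%

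*Protocol*

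**What the plan says.** The Power paragraph (Protocol, Statistical Analysis) assumes 220 first-degree alters in each arm and states its loss to follow-up as "degree alters per arm enroll, 10% attrition (month 6 retention in pilot was 96"%). For the control arm it takes "a 15% CC screening rate in control alters (based on pilot data"). Clustering enters through an "ICC=.01-.05 range to control for clustering within the alters of each index participant". Its conclusion on size is that "the effective sample size will be 200 (ICC=.05) or 216 (ICC=.01) per arm". From these it derives, for month 12 with 80% power and alpha .05, a detectable difference of 11 percentage points at ICC .01, and of 12 points, or an odds ratio of 2.0, at ICC .05.

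The pilot is described in section D.1. It enrolled "103 alters (58 intervention, 45 control") from 40 index participants and followed everyone for 6 months. Intervention alters "were much more likely to have been screened for CC at month 6", at 64% against 16%. No later pilot rate is reported.

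Section D.2, Study Overview, says the Preparation phase will "enhance usual care via provider training on the importance of recommending CC screening to clients". Section F.I gives the enrolment target as "based on average of 2.75 alters recruited per index participant", that is 440 in total.

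**The concern.** Two inputs do not match what the paragraph claims to compute.

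First, the time point. First-degree alters enter with no screening history, and the outcome is whether a previously unscreened alter gets screened. Once screened, an alter stays screened, so the cumulative control proportion at month 12 can equal the month-6 proportion or exceed it, but cannot fall below it. A 15% rate at month 12 therefore implies almost no control uptake in the second half-year, at clinics where providers have just been trained to recommend screening. For a comparison of proportions below 50%, a higher control rate enlarges the absolute difference that can be detected.

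Second, attrition is named as an assumption but does not appear to enter the stated effective sizes.

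At stake is how a modest or null month-12 result would be read. If the stated detectable difference is optimistic, a reader will take the trial to have excluded smaller effects than it can.

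**Working it through.** **Inputs.** 220 alters per arm, 10% attrition, ICC .01 to .05, control rate 15%, 80% power and alpha .05 (all from the Power paragraph); 80 index participants per arm and 2.75 alters per index (section F.I); 103 pilot alters from 40 index participants and 16% control uptake at month 6 (section D.1). The paragraph does not say whether alpha is two-sided; two-sided is used here.

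**Formulas.** Effective n = N / (1 + (m − 1) × ICC), with m alters per index. Power = Φ{ (|p2 − p1|√n − 1.96√(2p̄(1 − p̄))) / √(p1(1 − p1) + p2(1 − p2)) }, where p̄ is the mean of p1 and p2. The detectable difference is the value of p2 − p1 that gives 80%.

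**Step 1: reproduce the stated figures.** With m = 3 and all 220 alters kept, 220/(1 + 2 × .05) = 220/1.10 = 200 and 220/(1 + 2 × .01) = 220/1.02 = 215.7, which are the stated 200 and 216. Attrition has not been removed. At a 15% control rate these sizes give detectable differences of 11.3 and 10.8 points (11.9 and 11.4 with a continuity correction), consistent with the stated 12 and 11.

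**Step 2: deduct the stated attrition.** 220 × 0.90 = 198.
- m = 3: 198/1.02 = 194.1 and 198/1.10 = 180.0.
- m = 2.75 × 0.9 = 2.475: 198/1.01475 = 195.1 and 198/1.07375 = 184.4.

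At 15% control, the detectable difference is 11.5 points at ICC .01 and 11.8 to 12.0 at ICC .05. For 15% against 26% at n = 194.1: p̄ = .205, numerator .11 × 13.93 − 1.96 × .571 = .413, denominator .566, ratio .731, so power is 77%. For 15% against 27% at n = 180, power is 80%. With a continuity correction and m = 3 the detectable differences are 12.1 and 12.6, so the second stated figure is then missed as well.

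**Step 3: vary the month-12 control rate, after attrition.** These rates are assumptions. The top one extends the pilot's 16% per half-year at a constant rate: 1 − 0.84² = 29.4%.

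| Assumed control rate | ICC .01 (n 194–195) | ICC .05 (n 180–184) |
|---|---|---|
| 15% | 11.5 points | 11.8–12.0 points |
| 20% | 12.5 | 12.8–13.0 |
| 25% | 13.2 | 13.5–13.7 |
| 29% | 13.6 | 14.0–14.2 |

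**Step 4: the odds-ratio scale, at n = 184.** The detectable odds ratio is 2.08 at 15%, 1.96 at 20%, 1.88 at 25% and 1.84 at 29%. Power for an odds ratio of 2.0 is 75%, 83%, 87% and 89% respectively.

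**Step 5: pilot recruitment yield as a sensitivity case.** 103/40 = 2.575, so 80 × 2.575 = 206 per arm and 185.4 after attrition. With m = 2.575 × 0.9 = 2.3175, effective n is 185.4/1.0132 = 183 and 185.4/1.0659 = 174. At 15% control the detectable differences are 11.9 and 12.2 points. Without deducting attrition, the lower yield alone gives 11.2 and 11.6 to 11.7.

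**The case against.** A reader might infer that the true detectable difference is about 14 points because control uptake will reach 29%. The documents do not support that. The figure requires uptake to continue at the same rate for a second half-year, which is nowhere stated. The Protocol puts lifetime screening in Uganda at about 5%, so 16% within six months may already be front-loaded, prompted by being recruited by a screened friend and by the baseline survey. The pilot rate is also imprecise: about 7 of 45 has a Wilson 95% interval of roughly 8% to 29%. This objection stands. The control-rate part is a sensitivity question with a range, not a demonstrated error.

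A reader might also infer that 2.75 alters per index misreports the pilot. It does not: section F.I gives it as a planning average under a cap of three and never attributes it to the pilot. The phrase about pilot data in the Power paragraph belongs to the screening rate. The lower pilot yield alone moves the result by less than half a point.

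Nor does a higher control rate make matters worse on every scale. The paragraph also states its effect as an odds ratio, and Aim 1 uses logistic models; on that scale a higher control rate raises power, as step 4 shows.

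Finally, the pilot difference was 48 points. Even with 174 effective alters per arm, 29% against 50% would have about 98% power. The design is not shown to be underpowered for effects near the pilot's.

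None of this answers the attrition omission, which needs no outside rate.

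**Conclusion.** The point holds in a limited form. On the document's own inputs, the listed 10% attrition was not deducted. After deduction, 11 points at ICC .01 has about 77% power instead of 80%, and the detectable difference there is about 11.5 points. At ICC .05 the stated 12 points is just met, provided no continuity correction is applied.

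Separately, the month-12 statement rests on a month-6 control rate, with no justification for assuming that uptake then stops in clinics with enhanced usual care. This makes the percentage-point figure optimistic if control uptake continues. The size of that effect depends on a rate the documents do not give: at most about 2 further points over the assumed range of 15% to 29%, with the detectable odds ratio moving in the favourable direction. The results assume two-sided testing, equal arms and a simple two-proportion comparison with a design effect.

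**What to change.** Rewrite the Power paragraph for month 12. Deduct the 10% attrition before applying the design effect, giving effective sizes of about 194 to 195 (ICC .01) and 180 to 184 (ICC .05). Say that the 15% comes from a month-6 pilot result, and either justify it for month 12 or tabulate control rates from about 15% to 29%, labelled as assumptions. Report each row as both a percentage-point difference and an odds ratio. The two are not interchangeable as now written: 15% against 27% is an odds ratio of 2.10, whereas 2.0 corresponds to 11.1 points. Keep 2.75 alters per index as the base case and add the pilot's 2.575 as a sensitivity case.

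The cost is one revised paragraph and a slightly less favourable stated figure. Enrolment and design do not change.

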**D2.2.1 Multi-site RCT of CC-CCP.** At all 4 sites, 40 women screened for CC in the past year will enroll as index participants (n=160), with 20 randomly assigned to the intervention, and 20 to a wait-list usual care control. Individual randomization entails contamination risks, but statistical models suggest  $\geq 30\%$  of the control arm must receive the equivalent of a full-strength intervention for meaningful contamination. We decided against an attention control, because attention paid to intervention (index) participants would not impact alter behavior (primary outcome), and its policy implications would be less clear. The intervention arm will be divided into 2 groups of 10 (balanced on ages 25-35 and 36+) for receipt of the intervention. The control arm receives the intervention after the 12-month follow-ups. Each index participant will recruit up to 3 alters (total= ~440 alters; referred to as 1st degree alters) with no history of CC screening. All index and 1st degree alter participants will be followed up at months 6 and 12. At month 6, 1st degree alters will recruit up to 2 of their own alters (2nd degree alters; total= ~800) who they report targeting with advocacy and thereafter getting screened for CC; 2nd degree alters will be administered a single, brief phone interview.

**Eligibility criteria:** *Index participants:* female, age 25+ (the lower limit for recommended CC screening), screened for CC in past year (clinic records), and no advanced stage disease (12-month follow-up is feasible). *1st degree alters:* female, age 25+, and report no CC screening history. *2nd degree alters:* female and age 25+.

**Recruitment** of index and 1st degree alters will span 8 weeks (5 index and 14 alters per week) at each site. Clinic staff will contact eligible women who have been screened for CC in the past year to inform them of the study; if interested, the site coordinator will perform consent processes and formal eligibility screening. Eligible women who enroll will complete the baseline survey, followed by randomization as an index participant.

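### The stated effective sample sizes of 200 and 216 per arm omit the plan's own 10% attrition: power for 11 points falls to about 77%, and the 12-point claim has no margin left for group clustering.

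*Protocol*

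**What the plan says.** The power paragraph under Statistical Analysis (section D.2.2) lists its inputs in one sentence: 220 first-degree alters per arm, 10% attrition ("degree alters per arm enroll, 10% attrition"), an ICC of .01 to .05 for alters of the same index participant, and a 15% screening rate in control alters. The attrition figure is supported by past experience: "we have retained 90-94% over 12 months in past studies in Uganda". The result is that "the effective sample size will be 200 (ICC=.05) or 216 (ICC=.01) per arm".

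From this the protocol derives, at 80% power and alpha .05, a detectable difference of 11 percentage points at month 12 for ICC .01. For the higher ICC it says: "If ICC=.05, the detectable effect size is 12 percentage point difference (or odds ratio of 2.0".

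The Aim 1 analysis that follows names a second level of clustering: "We will account for correlation among participants in the same intervention group, and among alters referred by the same index". Section D2.2.1 explains where that level comes from. At each of the four sites, "The intervention arm will be divided into 2 groups of 10", which makes 8 groups in all.

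**The concern.** With a positive ICC, an effective sample size cannot exceed the number of people analysed. After 10% attrition, 198 alters per arm are left, so neither 200 nor 216 can follow from the inputs in the same sentence. The protocol also plans to adjust for intervention groups in the analysis but allows nothing for them in the power calculation.

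This is the only power statement for the primary outcome. If the trial finds a modest effect or none, readers will use these figures to judge what it could have detected, and they would credit it with somewhat more sensitivity than its own assumptions give.

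**Working it through.** **Inputs.** From the power paragraph: 220 alters enrolled per arm, 10% attrition, index-level ICC .01 or .05, control rate 15%, 80% power, alpha .05 (taken as two-sided; the protocol does not say). From section F, part I: an average of 2.75 alters per index. From section D2.2.1: at most 3 alters per index, and 8 groups of 10 index participants.

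**1. The plan's own figures.** Effective n = n / [1 + (m − 1) × ICC]. With n = 220 and m = 3:
- ICC .05: 220 / 1.10 = 200.0
- ICC .01: 220 / 1.02 = 215.7

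This reproduces the stated 200 and 216, with no attrition in them.

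**2. With attrition.** 220 × 0.90 = 198 per arm; alters retained per index = 2.75 × 0.90 = 2.475.
- ICC .05: 198 / 1.10 = 180.0 (m = 3); 198 / 1.07375 = 184.4 (m = 2.475)
- ICC .01: 198 / 1.02 = 194.1 (m = 3); 198 / 1.01475 = 195.1 (m = 2.475)

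Keeping 200 and 216 after 10% attrition would take about 242-245 enrolled per arm (for example 200 × 1.0875 / 0.9 = 241.7 and 216 × 1.02 / 0.9 = 244.8). The design's ceiling is 80 × 3 = 240.

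**3. Power and detectable difference.** Two-proportion test with pooled variance under the null: power = Φ{[d√n − 1.96 √(2p̄(1 − p̄))] / √(p₁(1 − p₁) + p₂(1 − p₂))}, with p₁ = .15, p₂ = .15 + d, and p̄ their mean.

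| Effective n per arm | Power at 11 points | Power at 12 points | Detectable difference at 80% |
|---|---|---|---|
| 216 (stated, ICC .01) | 81% | 87% | 10.8 points |
| 194-195 (after attrition) | 77% | 83% | 11.5 points |
| 200 (stated, ICC .05) | 78% | 84% | 11.3 points |
| 180-184 (after attrition) | 74-75% | 80-81% | 11.8-12.0 points |

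The test needs 211 per arm for 11 points and 180 per arm for 12 points.

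**4. Odds ratio.** 12 points from 15% gives (.27/.73) / (.15/.85) = 2.10. An odds ratio of 2.0 corresponds to 26.1%, or 11.1 points; its power is 79% at n = 200 and 74-75% at n = 180-184.

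**5. Group clustering, as a sensitivity range.** The protocol gives no group ICC, so the values below are assumptions. Each group holds about 198 / 8 = 24.75 retained alters. The design effect, in the intervention arm only, is 1 + 1.475 × ICC(index) + 22.275 × ICC(group).

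| Index ICC | Assumed group ICC | Intervention-arm effective n | Detectable difference | Power for the stated difference |
|---|---|---|---|---|
| .01 | .005 | 175.8 | 11.8 points | 75% (11 points) |
| .01 | .01 | 160.0 | 12.1 points | 73% (11 points) |
| .05 | .005 | 167.1 | 12.1 points | 79% (12 points) |
| .05 | .01 | 152.7 | 12.4 points | 77% (12 points) |
| .05 | .02 | 130.3 | 13.0 points | 74% (12 points) |
| .05 | .05 | 90.5 | 14.6 points | about 66% (12 points) |

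Control-arm effective n is 195.1 at index ICC .01 and 184.4 at .05. At index ICC .05, the 12-point claim falls below 80% power once the group ICC exceeds about .003. The range stops at group ICC = index ICC because two alters of the same index also share a group, so their correlation cannot be smaller than the group correlation.

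**The case against.** The strongest reply is that little turns on this. The 12-point claim survives attrition. The 11-point claim misses by half a point. The pilot difference (64% against 16%) is about four times either threshold, and no analysis or enrolment decision changes. All of that stands, and it is why the point is minor.

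A second reply is that 10% is the pessimistic end of the cited retention, and that chart data may supply the outcome for some alters who miss a survey. But 10% is the figure the paragraph adopts. Even at 94% retention, 220 × 0.94 = 206.8, and 206.8 / 1.02 = 202.7 and 206.8 / 1.10 = 188.0. Both are below the stated 216 and 200, and 202.7 is below the 211 needed for 11 points. If charts are meant to remove the attrition, it should not be listed as an input.

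A third reply concerns groups. Alters do not attend the sessions and are exposed only through their index participant, so a large group correlation among them is not self-evident, and the analysis handles it anyway. This stands as to size. It does not explain why a level of clustering that the analysis allows for is absent from the power calculation.

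A reader might also take the pairing of 12 points with an odds ratio of 2.0 as a separate substantive error. At the stated n = 200, the detectable difference is 11.3 points, an odds ratio of 2.02, so the mismatch is largely inconsistent rounding. It matters only because, after attrition, the two figures no longer both hold.

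**Conclusion.** The stated effective sizes are wrong on the plan's own inputs: they should be about 180-184 and 194-195, not 200 and 216. At ICC .01, the 11-point claim drops to about 77% power, with a detectable difference of about 11.5 points. At ICC .05, the 12-point claim holds at 80-81%, while an odds ratio of 2.0 has 74-75%. Group clustering is also missing. Under assumed group ICCs the detectable difference becomes about 11.8-12.1 points (index ICC .01) or 12.1-14.6 points (index ICC .05), and in the latter range the 12-point claim falls below 80% power.

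These results rest on a two-sided test, pooled variance without continuity correction, and equal arms. With a continuity correction, 12 points would fall to 76-77% after attrition, but that version gives only 78% for 11 points at n = 216, so it does not reproduce the stated claim.

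Three stronger readings are tempting but unsupported:
- That both stated differences are lost. Attrition alone removes only the 11-point one.
- That the trial is too small. Nothing here shows that, given the pilot effect.
- That the average of 2.75 alters per index is an error because the pilot had "103 alters (58 intervention, 45 control) who had never screened for CC were recruited" from 40 index participants (103/40 = 2.58). That is an openly stated planning assumption, and the pilot's intervention arm averaged 58/20 = 2.9.

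Severity: a minor correction to the stated power figures.

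**What to change.** In the power paragraph, state that after 10% attrition the effective sample size is about 194 (ICC .01) or 180 (ICC .05) per arm before group clustering. Give detectable differences of about 11.5 and 12 points, with odds ratios of about 2.0 and 2.1. Add one sentence with a sensitivity range for clustering in the 8 intervention groups, saying that the group ICC is assumed and keeping it no larger than the index ICC it is paired with. State whether alpha is two-sided.

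The cost is a few lines of text and a slightly less favourable power statement. Enrolment, follow-up and the Aim 1 analysis stay as they are.
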